## Abstract

**Background:**

In 2017, approximately 3.7 billion downloads of health apps were made on mobile phones and tablets. In this sense, a massive number of people could benefit by electronic mobile–based health interventions, making information available even with the lack of material and human resources. Hence, the use of electronic apps for dental education might be extremely useful for the prevention of early childhood caries (ECC).

**Objective:**

This study aims to evaluate the effectiveness of messages sent via mobile phones as an adjuvant method for the prevention of ECC.

**Methods:**

A single-blinded, randomized, and parallel-group clinical trial will be conducted with dyads of parents or caregivers and children aged between 36 and 60 months, recruited from kindergartens and schools of Bauru, São Paulo. The determination of sample size resulted in a total of 104 dyads of parents and children, considering a power of 80%, a significance level of 5%, and an attrition of 30%. This sample will be randomly assigned to test and control groups, being divided in 52 dyads per group according to the health literacy levels of parents and the age, gender, and oral health status of children. Every 2 weeks, only participants in the test group will receive messages via WhatsApp containing preventive and education-related ECC information. The dyads will visit the dentist every 3 months during a year for the assessment of primary outcomes (sugar consumption and the International Caries Detection and Assessment System, visible plaque, and community periodontal indices) and to receive dental care measures. Secondary outcomes (electronic health literacy and general perceived self-efficacy) will be determined only at baseline and after 12-month follow-up. The quality of randomization will be evaluated throughout the study, comparing the test and control groups systematically by Student t tests for continuous variables and chi-square tests for categorical variables. Listwise deletion method will be applied in cases of dropouts, if the missing values satisfy the criteria of missing completely at random; otherwise, multiple imputation data strategy will be conducted. The Kolmogorov-Smirnov and Levene tests will be used to determine the normality and homogeneity of data, respectively, which will indicate further statistical analyses for elucidating significant differences between groups (P<.05). A Student t test or Mann-Whitney U test will be employed for parametric or nonparametric analyses, respectively.

**Results:**

The project was funded in 2018, and enrollment was completed in August 2019. Allocation is currently under way and the first results are expected to be submitted for publication in 2020.

**Conclusions:**

The results will contribute to understanding the importance of educational mobile messages toward the adoption of healthy behaviors for the prevention of ECC in a given population.

**Trial Registration:**

Brazilian Registry of Clinical Trials Universal Trial Number U1111-1216-1393; http://www.ensaiosclinicos.gov.br/rg/RBR-2b6r7q/

**International Registered Report Identifier (IRRID):**

PRR1-10.2196/13656

## Introduction

### Background

The unprecedented spread of electronic technologies has facilitated the access of internet users to health information [1-3]. In 2017, approximately 3.7 billion downloads of mobile health apps were made to be used on cellphones and tablets [4]. In this sense, a large number of people could be benefited by health interventions using mobile devices, providing information on health care even in situations of low availability of material and human resources [5]. Currently, WhatsApp Messenger (WhatsApp Inc.) is one of the most popular mobile apps worldwide, with approximately 300 million users [6]. It connects people through free electronic messages, requiring only a Wi-Fi internet network [7,8]. WhatsApp Messenger has been shown to be a promising tool for the communication between patients and professionals, aiding in the spreading of health-related information [9].

In this context, the use of electronic apps for dental education might be extremely useful for the prevention of early childhood caries (ECC). It is defined as the presence of one or more decayed, lost, or restored surfaces found in deciduous teeth of children aged up to 71 months [10]. This disease affects about 621 million children, positioning it as the tenth most prevalent chronic disease out of 291 conditions of Global Burden of Disease Study [11]. ECC causes the impairment of mastication and speech, pain, psychological problems, and negative effects on the weight and growth of children [12-14]. In addition, approximately 94% of children diagnosed with ECC develop carious lesions in permanent dentition [15]. The identification of individual risk factors, parental counseling, and health promotion have played an important role in the prevention of ECC [16], contributing to the improvement of the quality of life of children and their families.

### Objectives

Therefore, new approaches are required to prevent ECC, aiming to improve the awareness about its consequences for deciduous and permanent dentitions, in addition to promoting the engagement of parents or caregivers with healthy behaviors toward the maintenance of oral health status of their children. In this sense, this study aims to assess the effectiveness of educational mobile messages sent via WhatsApp Messenger as an adjuvant method for the prevention of ECC in children of a given population. The null hypotheses for this study indicate that the educational mobile messages will not be effective for aiding in the control of dental plaque (H_0_), the decrease of sugar consumption (H_0_′), the maintenance of the International Caries Detection and Assessment System (ICDAS) indices (H_0_′′), and the improvement of parents’ electronic health (eHealth) literacy levels (H_0_′′′) after 12-month follow-up.

## Methods

### Overview

This study was reviewed and approved by the Council on Ethics in Human Research from the Bauru School of Dentistry (CAAE: 90563618.6.0000.5417), registered in the Brazilian Clinical Trials Registry (RBR-2b6r7q), and assigned with the universal trial number U1111-1216-1393. The peer review report is available in Multimedia Appendix 1.

### Study Design

This protocol describes a single-blinded, parallel, and randomized controlled trial (RCT) that will analyze the effectiveness of educational mobile messages as an adjuvant strategy for the prevention of ECC. The messages will be periodically sent via WhatsApp Messenger to parents or caregivers of children, who will be recruited from kindergartens and schools of Bauru, Brazil. The participants will be randomly allocated to 2 different groups (test and control). This RCT will be conducted according to the checklist and guidelines of the Consolidated Standards of Reporting Trials of Electronic and Mobile Health (CONSORT EHEALTH; beta version 1.5) [17]. Figure 1 depicts the synthesis of the design of this study.

**Figure 1 figure1:**
[figure not shown]
Study flowchart. CPITN: community periodontal index of treatment needs; eHealth: electronic health; eHEALS: The eHealth Literacy Scale; GSES: General Perceived Self-Efficacy Scale; ICDAS: International Caries Detection and Assessment System; VPI: visible plaque index.

### Eligibility Criteria

Dyads of parents and children will be recruited during visits to kindergartens and schools located in Bauru, Brazil, if satisfying the following inclusion criteria: children aged between 36 and 60 months; children at high risk of dental caries, according to the criteria described in the Caries Risk Assessment Form for 0- to 5-Year Olds [18]; children with a score ≤3, according to the criteria of ICDAS [19]; parents or caregivers with a mobile phone with internet access; parents or caregivers who accept to participate in all stages of research by signing a written informed consent form; and parents or caregivers who already have WhatsApp Messenger app installed on their smartphones, or those who agree to install it for the participation in the study.

The risk of dental caries will be based on the information collected during the anamnesis and clinical examination, which will be performed by a trained and calibrated dentist. Children will be examined in a dental clinic, using compressed air and artificial lighting, following the ICDAS criteria [19], the visible plaque index (VPI) [20], and the community periodontal index of treatment needs (CPITN) [21].

The oral hygiene level of children will be determined by the observation of visible plaque on the buccal dental surfaces of 6 deciduous teeth (#55, #53, #51, #71, #73, and #75) [20]. The periodontal health status of children will be assessed considering 3 parameters of analysis: presence of bleeding, detection of dental calculus, and depth of gingival sulcus [21]. According to Almeida et al [22], this study will classify deciduous teeth with 1 of 3 different scores: healthy (0), gingival bleeding (1), and presence of dental calculus (2).

### Electronic Health Literacy and Sociodemographic Questionnaire

The levels of eHealth literacy of parents or caregivers will be determined by the application of a previously validated Brazilian version of the eHealth Literacy Scale [23]. The eHealth Literacy Scale (eHEALS) will be applied by a trained professional, who provides the participants with a sheet containing 8 items related to skills needed to the adequate consumption of eHealth information. The answers of each item are arranged into a 5-point Likert scale, with options ranging from *completely agree* to *strongly disagree* [23]. The participants will be instructed to classify each item according to their own perception, achieving a total score varying from 8 to 40, with higher scores representing higher self-perceived eHealth literacy.

Finally, parents or caregivers will be invited to answer a questionnaire containing sociodemographic and child-related health information such as age, gender, race, and education level.

### International Caries Detection and Assessment System Training and Calibration

Overall, 2 investigators will be trained and calibrated for the use of ICDAS index according to the recommendations described below:

An official trainer will make a 4-hour presentation, including images, discussions on ICDAS codes, and examination protocols.A total of 2 days of training will be given with the same number of teeth coded with ICDAS between 1 and 5, including the clinical examination of patients with decayed and extracted teeth.Examination findings will be reviewed to verify the repeatability of tests and differences in the interpretation until consensus among examiners.A total of 2 days of concordance evaluation will be performed, using at least 20 patients with dental caries lesions with ICDAS ranging from 1 to 5 (kappa>0.65) [19].

### Randomization

Parent and child dyads will be randomly assigned to test or control groups, according to the parameters of stratification, as follows: health and eHealth literacy levels of parents or caregivers and the ICDAS index, age, and gender of children. The randomization will be performed using the platform Randomization.com [24], through different block sizes for the allocation of participants. The blinding of allocations will be guaranteed by using closed and opaque envelopes, which will be maintained confidential by an independent researcher.

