### Sample Size

The calculation of this sample size was performed using the Open Source Epidemiologic Statistics for Public Health, following the criteria and outcomes described by Zotti et al [25]. It resulted in a total of 104 dyads of parents and children, considering a power of 80%, a significance level of 5%, and an attrition of 30%.

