## Results

At this moment, 104 dyads have already been recruited. The parents or caregivers have responded the questionnaires, while children are being examined to determine their baseline oral health status. From August, 2019, dyads will be allocated to control or test groups. The parents or caregivers will receive the first electronic message after 15 days of allocation. The first results related to oral health status of children are expected to be obtained in November, 2019. The data collection will be performed during 12 months, between August 2019 and 2020.

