Parents and caregivers seem to play an important role in the management of chronic diseases of their children [47,48], especially when these diseases affect children under 3 years, which is observed with ECC. Mobile technologies have become important resources to empower patients to be active on their own conditions through shared decision-making process [49-52]. Nevertheless, parents and caregivers could be less used to electronic devices and even less to download apps for their mobiles or tablets [47,53]. Hence, ECC-related information delivered via WhatsApp Messenger could be an alternative to engage parents or caregivers in a healthy lifestyle, contributing to a better patient-professional relationship. This app is a low-cost instant-messaging platform very popular in Latin America, and more specifically in Brazil, where 56% of the population uses it frequently [54]. According to Ojeda et al [55], WhatsApp Messenger demonstrated its effectiveness for contacting patients, independently of their education level, making it a reliable source of information and an easy way for patient-professional interaction. A previous study reported a significant reduction of dental plaque in adolescents after using WhatsApp Messenger as an adjuvant for the prevention of oral diseases [56]. However, to our knowledge, there is no evidence showing the effect of educational electronic messages sent to parents or caregivers on the prevention of ECC.

These outcomes will demonstrate the influence of educational mobile messages sent via WhatsApp Messenger on the different parameters of oral health status of children, such as biofilm accumulation, dental demineralization, gingival health, and sugar consumption. In addition, the effect of this study protocol on the levels of eHealth literacy and perceived self-efficacy of parents or caregivers will be elucidated. All aforementioned analyses will consider the effect of possible sociodemographic confounding factors, after stratifying and controlling participants according to eHealth literacy levels of parents or caregivers and the ICDAS index, age, and gender of children.

The evidence produced in this study can support the development of digital strategies to be applied in ECC preventive programs, considering their 3 main advantages: scalability, cost-effectiveness, and empowerment of laypersons for self-dental care.

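### The stratification factors are listed in three different ways, and with 104 dyads the blocked scheme neither assures 52 per group nor gives more than partial control, while the named tests are unadjusted

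*Protocol article*

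**What the plan says.** Three places in the Protocol article describe the factors that govern allocation.

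- Abstract, Methods: the sample is assigned to two groups, "being divided in 52 dyads per group according to the health literacy levels of parents and the age, gender, and oral health status" of the children. That is four factors, with health literacy as the literacy factor.
- Randomization: the stratification parameters are "health and eHealth literacy levels of parents or caregivers and the ICDAS index, age, and gender of children". That is five factors, with both kinds of literacy. Allocation uses blocks of varying size, and the sizes are not stated.
- Discussion: the analyses are said to take account of sociodemographic confounding after participants have been stratified and controlled "according to eHealth literacy levels of parents or caregivers and the ICDAS index, age, and gender of children". That is four factors, with eHealth literacy only.

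The section on eHealth literacy describes one literacy instrument, eHEALS, scored 8 to 40. No cut-points are given for literacy, ICDAS or age. Eligibility restricts ICDAS to 3 or lower and age to 36 to 60 months.

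On sample size the article says: "It resulted in a total of 104 dyads of parents and children". For group comparisons, Data Analysis names a Student t test or a Mann-Whitney U test, without covariates.

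On timing, Results says that 104 dyads are recruited, that children are still being examined, and that "From August, 2019, dyads will be allocated to control or test groups". The Abstract's Results paragraph says that allocation is already in progress.

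**The concern.** Two things look wrong. First, a reader cannot tell which scheme was used. The section that governs allocation has the longest list, and one of its factors, general health literacy, has no described source of data.

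Second, permuted blocks balance the arms only when blocks are completed within strata. Four or five factors divide 104 dyads into many small strata, and many of these end inside an incomplete block. The leftover imbalances add up across strata, so a 52:52 split does not follow from the method described.

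At stake is the control of baseline differences that the Discussion attributes to stratification. One of the factors, ICDAS, is also a primary outcome measure. If balance is only partial and the test is unadjusted, the remaining imbalance is left in the comparison.

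**Working it through.** **Inputs from the article.** 104 dyads in total, 52 per group, 30% attrition, 80% power, 5% significance level; five factors (Randomization) or four (Abstract, Discussion); ICDAS codes up to 3 at entry.

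**Assumptions, because the article does not give these.** At least two levels per factor, equally frequent and independent; blocks of 4 and 6, or of 2 and 4, chosen at random.

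**Step 1: strata.** Number of strata = product of the levels; average size = 104 / strata.

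- Five binary factors: 2^5 = 32 strata; 104/32 = 3.25.
- Four binary factors: 2^4 = 16 strata; 104/16 = 6.5.
- Five factors with ICDAS kept at four codes (0 to 3): 2^4 × 4 = 64 strata; 104/64 = 1.6.
- Four factors with ICDAS at four codes: 2^3 × 4 = 32 strata; 3.25.

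Two levels is the minimum for a factor, so 3.25 and 6.5 are upper bounds on the average for five and four factors.

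**Step 2: arm sizes.** Stratified permuted blocks were simulated, 8,000 runs per setting (Monte Carlo error about 0.5 point or less). The simple randomisation percentages are exact binomial values.

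| Scheme | Blocks | Exactly 52:52 | Arms differ by 8 or more | SD of difference |
|---|---|---|---|---|
| 64 strata | 4/6 | 10.3% | 36.8% | 7.9 |
| 64 strata | 2/4 | 12.4% | 28.6% | 6.6 |
| 32 strata | 4/6 | 13.3% | 24.0% | 6.0 |
| 32 strata | 2/4 | 16.5% | 15.0% | 4.9 |
| 16 strata | 4/6 | 19.5% | 8.5% | 4.1 |
| 16 strata | 2/4 | 23.7% | 3.6% | 3.4 |
| 4 strata (two binary factors) | 4/6 | 39.0% | under 0.1% | 2.0 |
| Simple randomisation | none | 7.8% | 49.3% | 10.2 |

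**Step 3: balance on a factor.** The mean absolute difference between arms within one level of a binary factor is about 2.7 to 3.4 dyads with five binary factors and 1.9 to 2.3 with four. Under simple randomisation it is 5.7.

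**Step 4: completed blocks.** With 32 strata, about 26% of strata complete at least one block if blocks are 4/6, and about 62% if they are 2/4. With 16 strata the figures are 77% and 94%.

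**Step 5: power.** The article gives no effect size, so the 104 cannot be rebuilt from its own inputs. For scale only: 52 × 0.7 = 36.4 evaluable per arm. Taking 36 per arm, 80% power and a two-sided 5% level (sidedness is not stated), the implied standardised difference is (1.960 + 0.842) × √(2/36) = 0.66. With 30% attrition in each arm, power is 80.4% at 52/52, 80.1% at 47/57 and 79.7% at 45/59.

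**The case against.** The other side has good arguments, and several of them stand.

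- **Health literacy.** A reader might infer that it is never measured, so that the factor cannot be implemented. The article does not support that. It condenses a fuller protocol, describes only eHEALS, and does not say that no other instrument is used. The term may also be shorthand for eHealth literacy, since the Discussion names only the latter. What stands is an inconsistency and a factor without a described instrument.
- **Stratum size.** A reader might take two or three dyads per stratum as the design. That counts health literacy as a working fifth factor. On the four-factor reading with binary levels the average is 6.5. Exact 52:52 is still not assured there, but large imbalances are uncommon.
- **Blocks.** A reader might conclude that most strata never complete a block, so that the scheme amounts to simple randomisation. With blocks of 2/4 and 32 strata a majority do complete one, and in every setting shown the stratified scheme balances better than simple randomisation.
- **Consequences.** Chance imbalance does not bias a randomised comparison, and the loss of power is negligible. Both points are right.
- **Analysis.** The Discussion promises to consider confounding, and an adjusted model may be set out in a document not shown. But the tests that this article names carry no covariates.
- **Timing.** The two statements on timing leave it open whether every child is examined before allocation starts, so a remedy that depends on this must be conditional.

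**Conclusion.** The point holds in a limited form. The three factor lists conflict and need to be reconciled; this rests on the text alone. The bounds on average stratum size (3.25 for five factors, 6.5 for four) need only two or more levels per factor. The split probabilities, about 13 to 17% for exact 52:52 with 32 strata and 20 to 24% with 16, also depend on the assumed equal frequencies and block sizes.

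The scheme as written gives useful but partial balance, and 52 per group is a target that it does not guarantee. The power cost is under 1 point, so neither the validity nor the power of the trial is in question. What suffers is the reproducibility of the allocation and the control of baseline factors credited in the Discussion. It is worth correcting because the correction is cheap.

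**What to change.** 1. State one factor list, the same in the Abstract, Randomization and Discussion. Drop health literacy unless an instrument for it is named. Give the levels and cut-points.
2. If allocation has not begun, either stratify on one or two factors with stated cut-points, for example ICDAS (0 versus 1 to 3) and eHEALS (median split), or allocate the full recruited list at once, after the baseline examinations, with 52:52 fixed. With two binary factors the arms would differ by 8 or more in under 0.1% of runs (blocks 4/6), but exact 52:52 still occurs in only 39%; only the whole-list option fixes it. The algorithm used for that is a matter of preference.
3. If allocation has begun, leave it as it is. Report the factors, cut-points and arm sizes actually used, and describe 52 per group as a target.
4. In either case, replace the unadjusted t or Mann-Whitney comparison with a model that adjusts for the baseline value of the outcome and for the stratification factors (eHEALS, ICDAS, age, gender). All of these are already collected. For the ICDAS outcome, the baseline value and the stratification factor are the same measure and enter once.

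The cost is a few lines of text and slightly more allocation and analysis work. No extra data or participants are needed.

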### Sample Size

The calculation of this sample size was performed using the Open Source Epidemiologic Statistics for Public Health, following the criteria and outcomes described by Zotti et al [25]. It resulted in a total of 104 dyads of parents and children, considering a power of 80%, a significance level of 5%, and an attrition of 30%.

